### Data Analysis

Descriptive statistics will be estimated with respect to key feasibility variables. At baseline, rates of practice and patient recruitment, prevalence of problem drug use at participating practices, and baseline prevalence of problem alcohol use among problem drug users will be estimated. Process and fidelity evaluation of pilot educational intervention will be explored. Practice/patient retention rates, prevalence of problem alcohol use among problem drug users, and confounding factors such as practice busyness or person who performed SBI will be analyzed for outcome measures.

SPSS v20 and R software will be used for analysis by the HRB Center for Support and Training in Analysis and Research.

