**Methods:**

Psychosocial intervention for alcohol use among problem drug users (PINTA) is a pilot feasibility study of a complex intervention comprising SBI for problem alcohol use among problem drug users with cluster randomization at the level of general practice, integrated qualitative process evaluation, and involving general practices in two socioeconomically deprived regions.
Practices (N=16) will be eligible to participate if they are registered to prescribe methadone and/or at least 10 patients of the practice are currently receiving addiction treatment. Patient must meet the following inclusion criteria to participate in this study: 18 years of age or older, receiving addiction treatment/care (eg, methadone), or known to be a problem drug user. This study is based on a complex intervention supporting SBI for problem alcohol use among problem drug users (experimental group) compared to an “assessment-only” control group. Control practices will be provided with a delayed intervention after follow-up. Primary outcomes of the study are feasibility and acceptability of the intervention to patients and practitioners. Secondary outcome includes the effectiveness of the intervention on care process (documented rates of SBI) and outcome (proportion of patients with problem alcohol use at the follow-up). A stratified random sampling method will be used to select general practices based on the level of training for providing addiction-related care and geographical area. In this study, general practitioners and practice staff, researchers, and trainers will not be blinded to treatment, but patients and remote randomizers will be unaware of the treatment.

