#### Phase 2: Exploratory Study

A pilot study in addiction clinics showed that SBIs are effective in reducing alcohol consumption among opiate-dependent patients [16]. There is a current proposal to establish the acceptability and effectiveness of the intervention by conducting a feasibility study in primary care.

This protocol reflects the development and piloting phases of the MRC’s “Framework for the design and evaluation of complex interventions to improve health” [20,22]. The present study will provide key parameters regarding the feasibility and acceptability of the intervention to patients and practitioners. As such, this research is essential to inform the design and conduct of a larger cluster randomized controlled trial (RCT).

The specific objectives of the study are as follows. First, this study aims to develop a complex intervention that will enhance SBI for problem alcohol use among problem drug users in primary care. This study will help to establish the practical feasibility and acceptability of complex intervention (1) by conducting a pilot study (with randomization at the level of practice), (2) exploring the feasibility and acceptability of the intervention under study and related research procedures to GPs, practice nurses, and patients, and (3) exploring the fidelity of the interventions as delivered in practice. Finally, we can decide to inform the subsequent design of a definitive cluster RCT by describing the optimum configuration of the complex intervention and by estimating the key parameters in such a trial (ie, practice/patient recruitment and retention rates, intraclass correlation coefficient for primary outcome measures, and the likely effect of intervention under study on these measures).

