## Methods

### Overview of Study Design

Psychosocial intervention for alcohol use among problem drug users (PINTA) is a pilot feasibility study of a complex intervention to promote SBI for problem alcohol use among problem drug users, with cluster randomization at the level of general practice, and integrated qualitative process evaluation, involving general practice in two regions.

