Patients who consult a GP taking part in the study, and who in the clinical opinion of the GP are eligible to participate in the study (see inclusion criteria above), will be given written information on the study. Those interested in participating will be invited to meet a researcher who will be at the practice during the recruitment period. At this meeting, interested patients will be given further information on the study and will have an opportunity to ask questions from the researcher. If patients consent to participate, they will be asked to sign a consent form and complete a self-/interviewer-administered questionnaire that includes problem alcohol use and other outcome measures, if necessary with the assistance of the researcher at T1 (ie, Time 1, at baseline) and T2 (ie, Time 2, at 3 months follow-up). This applies to patients in both the intervention and control groups.

Following completion of the self-/interviewer-administered questionnaire with the researcher, patients in the intervention practices will be screened for problem alcohol use and delivered the brief intervention by their GP/practice team (at their earliest convenience). Patients in the control arm will receive the “Less is more” leaflet (a guide to rethinking your drinking, HSE, 2008) from the researcher. A “thank you” letter will be sent to all GPs and patients within 2 weeks of receiving completed study instruments/intervention. A reminder letter will be sent to all GPs and patients 5 weeks before the follow-up assessments, informing them of the anticipated time/date of their appraisal. Figure 1 presents the CONSORT diagram of participant flow and follow-up.

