### Intervention

#### Overview

A staggered intervention design will be adopted, whereby participating practices randomized to the intervention arm of the study will be provided with the complex intervention for the duration of the study period, while practices randomized to the control arm of the study will provide usual care to patients for the duration of the study and will be provided with the complex intervention thereafter (ie, delayed intervention). Such an approach was used successfully in our previous cluster randomized controlled study to improve screening for hepatitis C among problem drug users attending general practice in Ireland [25].

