#### Experimental Intervention

A complex intervention will be delivered to practices assigned to the intervention arm at two levels: (1) practice level and (2) patient level.

Interventions that are delivered at practice level include CME/CPD-accredited education delivered both internally (practice-based academic detailing) and externally (seminar), dissemination of clinical guidelines, other resources to facilitate implementation at practice level (eg, contact details/referral information for local services).

All practices will participate in the external education (seminar). Internal education (practice-based academic detailing) will be offered on as-needed basis, depending on practice resources and experience with SBI [35]. Academic detailing and support will be available to practices during the 3 months study period. The number and duration of these visits will be used to predict the level of support for a future definitive RCT.

At patient level, SBI (10-15 minutes) is delivered to patients.

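### Who performed SBI is labelled a confounder, but it is settled after randomisation and is part of the intervention, so it should not be adjusted for between arms

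*Protocol article*

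**What the plan says.** The Data Analysis section of the protocol article says that "confounding factors such as practice busyness or person who performed SBI will be analyzed for outcome measures". It gives no model. The sentence just before it deals separately with process and fidelity evaluation.

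Other sections fix what SBI is in this trial:

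- Design (Overview of Study Design): a pilot "with cluster randomization at the level of general practice, and integrated qualitative process evaluation".
- Intervention arm (Identification and Recruitment of Patients): after the baseline questionnaire, "patients in the intervention practices will be screened for problem alcohol use and delivered the brief intervention by their GP/practice team". Experimental Intervention lists this as the second level of the intervention: "At patient level, SBI (10-15 minutes) is delivered to patients".
- Control arm: "Patients in the control arm will receive the “Less is more” leaflet" from the researcher, and under Intervention, Overview, "practices randomized to the control arm of the study will provide usual care to patients for the duration of the study".
- Use of the results: the abstract states "Secondary outcome includes the effectiveness of the intervention on care process (documented rates of SBI) and outcome", the latter being problem alcohol use at follow-up. Phase 2: Exploratory Study lists "the likely effect of intervention under study on these measures" among the parameters to be estimated for a definitive cluster trial.

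**The concern.** A confounder of a randomised comparison must be a characteristic that exists apart from the allocation and could differ between arms by chance. The identity of the SBI provider is not of that kind. It comes into being when the intervention is delivered, and in the control arm it has no trial counterpart. Adjusting for it takes part of the intervention's own effect out of the arm coefficient and compares groups selected by what happened after allocation.

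For the care-process outcome the difficulty is sharper. A provider exists only where SBI took place, so adjusting documented SBI rates for provider conditions on the outcome itself.

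What is at stake is the effect estimate to be carried into the design of the definitive trial. If it comes from a provider-adjusted model, a useful intervention could look ineffective or harmful.

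**Working it through.** The protocol states no figure for this point, so there is none to reproduce. The check is to see what the arm coefficient estimates once provider is in the model.

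**Inputs from the protocol**
- 160 patients in 16 practices, and a 75% target for SBI receipt in the intervention arm (Power Calculations and Sample Size Estimates).
- About 80 intervention patients: Qualitative Evaluation equates a 20% sample with 16 patients, and 16 / 0.20 = 80. That leaves 80 controls.
- 35% prevalence of problem alcohol use, from the earlier national survey (Previous Work in Ireland).

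**Assumptions, not in the protocol**
- SBI lowers the risk of problem alcohol use at follow-up by d = 10, 15 or 20 points in those who receive it. Without SBI the risk stays at 35% on average.
- Control patients receive SBI in usual care at 0% or 10%.
- Receipt is either unrelated to severity, or is 60% in the more severe half (risk 50%) and 90% in the less severe half (risk 20%), which averages 75%.
- Linear model, clustering ignored, provider coded GP / other staff / none.

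**Step 1. Randomised comparison without provider.** Effect = −(receipt in intervention − receipt in control) × d.
- 0% control SBI: −0.75 × 0.10, 0.15, 0.20 = −0.075, −0.113, −0.150.
- 10% control SBI: −0.65 × 0.10, 0.15, 0.20 = −0.065, −0.098, −0.130.

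**Step 2. Provider added, no control SBI.** Every patient with a provider is in the intervention arm, so the provider terms absorb the receivers. The arm coefficient becomes the risk in intervention non-receivers (25% of 80 = 20) minus the risk in controls (80).
- Receipt unrelated to severity: 0.35 − 0.35 = 0, whatever the value of d.
- Receipt related to severity: the severe share of non-receivers is 0.40 / (0.40 + 0.10) = 0.80. Their risk is 0.80 × 0.50 + 0.20 × 0.20 = 0.44, so the coefficient is 0.44 − 0.35 = +0.09.

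**Step 3. Provider added, 10% control SBI, receipt related to severity in the intervention arm only.** The coefficient averages two contrasts, weighted by n1·n0/(n1 + n0).
- Non-receivers: +0.09, weight 20 × 72 / 92 = 15.7.
- Receivers: the severe share in the intervention arm is 0.60 / (0.60 + 0.90) = 0.40, giving risk 0.32 − d against 0.35 − d in controls, a contrast of −0.03. With receivers split evenly between two provider types, the weight is 2 × (30 × 4 / 34) = 7.1.
- Result: (15.7 × 0.09 − 7.1 × 0.03) / 22.8 ≈ +0.05.

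**Step 4. Simulation under the same assumptions** (16 practices of 10, 8 per arm, 3,000 runs per scenario). Mean arm coefficients for d = 10 / 15 / 20 points:

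| Control SBI | Receipt and severity | Without provider | With provider |
|---|---|---|---|
| 0% | unrelated | −0.072 / −0.112 / −0.150 | 0.004 / 0.001 / −0.001 |
| 10% | unrelated | −0.062 / −0.097 / −0.132 | 0.004 / 0.003 / −0.003 |
| 0% | related | −0.075 / −0.113 / −0.149 | 0.090 / 0.090 / 0.091 |
| 10% | related | −0.067 / −0.096 / −0.131 | 0.051 / 0.054 / 0.054 |

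The standard deviation of the coefficient rises from about 0.07 without provider to between 0.09 and 0.13 with it.

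**Step 5. When the coefficient cannot be estimated.** With none as a category, arm is an exact sum of the provider indicators only if every intervention patient receives SBI and no control does. With 100% receipt and no control SBI, all 200 simulated fits were rank-deficient. At 75% receipt none were.

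**The case against.** The strongest reply is that the harmful model is not in the document. The verb used for provider is also used for retention rates and prevalence, which nobody would take as covariates. Provider may simply be explored as an influence on implementation, and model details commonly belong in an analysis plan that is not shown. This stands in part: the harm is conditional on provider entering a between-arm model. It does not remove the point. The confounder label is stated, process and fidelity evaluation already has its own sentence, and under Recruitment and Random Selection of Practices the authors use the same label for GP level, which they say they will bring into the analysis. That use is sound, because GP level precedes randomisation and is a stratification factor.

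Three stronger readings are tempting, and the document does not support them.

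- *The treatment effect would be impossible to estimate.* With non-receivers coded as none, this needs full receipt and no control SBI. The protocol's own target is 75% receipt.
- *All 80 or so controls have no value and would drop out.* Control practices give usual care, which may include SBI. Documented SBI is an outcome, and the record review in Table 1 covers current and previous screening and intervention. Losing the whole control arm would also require that absent providers be left missing and those patients excluded, which the protocol does not say.
- *Practice busyness has the same defect.* The protocol does not say when busyness is measured. Table 1 includes a baseline staff questionnaire on practice details, and a measure taken before allocation would be acceptable.

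It is also fair to say that feasibility and acceptability are primary, that the study declares itself unpowered for effectiveness, and that nothing prevents an unadjusted or level-adjusted estimate from being reported as well. This limits the severity but leaves the classification wrong.

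**Conclusion.** The point holds in conditional form. Calling the SBI provider a confounder is wrong on the protocol's own description of the intervention. A between-arm estimate adjusted for it would not be an estimate of the intervention effect. Under the stated assumptions, a true effect of 6.5 to 15 points becomes about zero when receipt is unrelated to severity, and becomes 5 to 9 points in the wrong direction when more severe patients receive SBI less often. These sizes illustrate the mechanism. They depend on assumed benefits and receipt patterns and on ignoring clustering, and they do not predict this trial's result.

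Severity is moderate. No primary conclusion rests on the adjusted estimate, but the likely effect is one of the parameters that the pilot is meant to hand on.

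**What to change.** Change one sentence in Data Analysis:

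- Remove the SBI provider from the confounders for between-arm outcome comparisons, and analyse it within the intervention arm as process and fidelity data. Provider is not randomised and may follow practice, so differences in outcome by provider should be reported as descriptive.
- State that between-arm estimates are adjusted only for variables fixed before randomisation: GP level and region. Baseline AUDIT may be added for precision; it is optional and not needed to cure this error.
- Use practice busyness in the between-arm analysis only if it is recorded before allocation, and say when it is recorded. Otherwise treat it as process data too.

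The cost is a wording change, with no new data and no change to sample size or procedures.

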### Qualitative Evaluation

A parallel qualitative evaluation will also be conducted with patients and health care professionals.

With regard to health care professionals, open-ended questions will be asked eliciting information on staff attitudes toward alcohol SBI, previous practice of alcohol SBI, preparedness to undertake these activities, the training required to implement SBI, the suitability of each site to provide SBI, and other barriers to effective implementation [34].

With regard to patients, among a 20% purposive sample (estimated N=16) of patients in the intervention practices, we will also explore patients’ satisfaction with and experience of intervention and care related to problem alcohol use in the preceding 3-6 months. Interviews will be done by researcher via telephone, postal questionnaire, or in person. Prior to the interviews, the participant will be informed of the interview purpose, the interview procedure, and the use of the findings. The participant will then be invited to sign an additional consent form and the interview will commence.

Qualitative data analysis will be systematic and organized to easily locate information within the dataset when tracing results, providing examples in context [43]. The qualitative research software Nvivo v8 will be used to facilitate the coding. Thematic analysis will be used to analyze qualitative data. This approach has many benefits for such an interpretive study, as it is a “method for identifying, analyzing, and reporting patterns (themes) within data” [43].

### Ethical Considerations

Ethical approval has been obtained from the Research Ethics Committee of the Irish College of General Practitioners (Protocol Reference: [name], 2012 Nov 29). Research carried out on humans in this study is in compliance with the Helsinki Declaration. The protocol follows the checklist of items to consider for inclusion in a report of a pilot studies [44], adopted from the CONSORT statement [45,46].

A two-stage procedure to obtain informed patient consent to participate in the study will be used during the study. Patients who consult a GP taking part in the study, and who in the clinical opinion of the GP are eligible for the study, will be given written information on the study (brief study information sheet). Those interested in participating will be invited to meet a researcher who will be at the practice during the recruitment period. At this meeting, interested patients will be given further information on the study and will have an opportunity to ask questions from the researcher. When all issues have been explained to patients’ satisfaction, they will be asked to indicate consent to participate in the study by signing a consent form and this procedure will be witnessed by a third party. The standard patient consent form for participation in nonclinical trials, developed by the Research Ethics Committee of the Irish College of General Practitioners, will be used in the study. Participation in the study will be on a voluntary basis. No inducements to participate will be offered to patients, and refusal to participate will not compromise patient care.

Potential adverse effects of the intervention will be explored in the qualitative interviews with patients and practitioners.

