### Study Population

#### Recruitment and Random Selection of Practices

The following practices will be invited to participate, given written information on the study and their interest in participating:

All practices in two regions—Health Services Executive (HSE) Midwest and Dublin Mid-Leinster regionsAll practices that have been involved in previous related research with our group [18,23-29]General practices in the study regions that are affiliated with two of the Ireland’s six medical schools [30,31]

Practices will be eligible to participate if they are registered to prescribe methadone and/or have at least 10 patients currently receiving addiction-related care.

Of those who confirm their *interest* in the study and who are eligible to participate, a stratified random sampling technique will be used to select 16 practices.

Sampled GPs will be contacted about their participation, given further information on the study (eg, what their involvement will entail) and consulted about patient recruitment. The research team will telephone those not replying. Each practice will be visited by the principal investigator or lead researcher and provided with the information about the research program.

To ensure comparability between intervention and control groups for key practice characteristics, a restricted allocation involving stratified approach to randomization will be adopted. Prior to randomization, GPs who express their interest in participating will be grouped according to the level of training in providing addiction-related care (level 1 and 2), geographical location (Dublin/Midwest), with 16 randomly selected GPs using an independent remote randomization service.

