#### Power Calculations and Sample Size Estimates

The goals of this study are to examine the feasibility, acceptability, and effectiveness of the complex intervention. As observed in previous studies, with respect to the feasibility component, the present study aims to achieve 20% recruitment/consent rate (ie, number of invited GPs who confirm their interest in the study) [19], 75% participation rate (ie, the number of participants allocated to the intervention arm who will receive/complete SBI) [5], and 75% retention or follow-up rate [5].

Based on the recommendations for good practice in pilot studies [32,33], we estimate that 160 patients (attending 16 general practices) will be adequate to calculate the actual recruitment and retention rates (ie, *feasibility*) for a sample of patients recruited in primary care and provide data on *acceptability* of study processes and outcome measures, which will inform a future definitive trial. This pilot study is not powered to determine effectiveness of SBI on reduction of alcohol consumption among problem drug users. The proportion of patients who reduce their alcohol consumption will be used to predict the sample size and length of follow-up for a future definitive RCT.

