### Data Collection

#### Timeline

At baseline, demographic details and data on primary/secondary outcome measures will be collected by reviewing clinical records and by patients completing study instruments. At follow-up, data will again be collected by reviewing clinical records and by patients completing study instruments. Participants will be invited to complete a follow-up interview with a researcher to include primary/secondary outcome measures. A purposive sample of patients in the “intervention” arm will be interviewed regarding their experience in care for alcohol-related problem in the preceding 3 months.

Quantitative data will be collected at baseline (T1) and at 3 months follow-up (T2) using clinical records (T1, T2), self-/interviewer-administered questionnaires and semistructured interviews (patients, T1, T2), and self-administered questionnaires, including open-ended questions (practitioners, T2).

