##### Patient Measures

These measures include indirect examination and direct examination. At baseline and follow-up, the study battery will include the following: (1) Alcohol Use Disorders Identification Test (10 items) (AUDIT), (2) Maudsley Addiction Profile (MAP), and (3) Readiness Ruler.

AUDIT developed by the World Health Organization is used to identify a continuum of problem alcohol use [21,38].

MAP is a brief, structured questionnaire for treatment outcome research and measures problems specifically in four areas: substance use, health risk behavior, physical and psychological health, and personal/social functioning [18,39].

Readiness Ruler will assess patient’s motivational state regarding changing their drinking behavior [41].

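### The stated adverse-effect assessment is uncontrolled, rests on about 16 selected intervention-arm patients, and cites practitioner interviews that the data-collection sections describe as questionnaires

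*Protocol article*

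**What the plan says.** All references are to the protocol article.

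- **Ethical Considerations** names one method for harms: "Potential adverse effects of the intervention will be explored in the qualitative interviews with patients and practitioners".
- **Patient interviews.** Qualitative Evaluation places these "among a 20% purposive sample (estimated N=16) of patients in the intervention practices". Timeline agrees on the arm and the sampling: "A purposive sample of patients in the “intervention” arm will be interviewed regarding their experience in care for alcohol-related problem in the preceding 3 months". The stated content in Qualitative Evaluation is "we will also explore patients’ satisfaction with and experience of intervention and care related to problem alcohol use in the preceding 3-6 months". Harm is not named.
- **Practitioners.** Timeline lists "self-administered questionnaires, including open-ended questions (practitioners, T2". Table 1 likewise collects practitioners' experience of the intervention as free text in a follow-up questionnaire. Qualitative Evaluation refers to open-ended questions on attitudes, earlier practice, preparedness, training, site suitability and barriers. Harm is not among these topics, and no section describes a practitioner interview.
- **Data in both arms.** Under Identification and Recruitment of Patients, intervention and control patients alike complete the study questionnaire at baseline (T1) and 3 months (T2). The battery includes AUDIT and MAP. Patient Measures says that MAP "measures problems specifically in four areas: substance use, health risk behavior, physical and psychological health, and personal/social functioning". Table 1 places MAP under effectiveness, as a measure of other drug use, and does not label it a harm measure.
- **Size.** Power Calculations and Sample Size Estimates says "we estimate that 160 patients (attending 16 general practices) will be adequate to calculate the actual recruitment and retention rates" and sets a 75% retention target.

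**The concern.** The point is about the method the article chooses, not about detail it leaves out. The route named for adverse effects has three weaknesses.

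1. It reaches about one in five intervention patients, chosen purposively. A count from it has no usable denominator.
2. Controls are not asked. In a population where drug use and ill health are common, an event reported in an interview cannot be set against the background frequency.
3. Its practitioner half refers to an instrument that the data-collection sections do not contain. The questionnaires they do contain are not said to ask about harm.

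The study is presented as the first of its kind in primary care and is meant to inform a definitive cluster trial. A pilot is the natural place to test how harms will be captured, and this plan would hand on little about that.

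**Working it through.** **Inputs from the article:** 160 patients in 16 practices; 75% retention; a 20% purposive sample, estimated N=16.

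**Assumptions:** 1:1 allocation, because the text says only that "a restricted allocation involving stratified approach to randomization will be adopted" and gives no ratio; true harm rates of 2%, 5% and 10%, for illustration; an intraclass correlation (ICC) of 0 or 0.05.

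**Step 1: reproduce N=16.** 160 / 2 = 80 patients per arm, and 0.20 × 80 = 16. This matches. The alternatives do not: 20% of all 160 is 32, and 20% of the 60 intervention patients retained is 12. So the interviews cover 16 of about 80 intervention patients and no controls.

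**Step 2: chance of including at least one affected patient.** The formula is 1 − (1 − p)^n. With 75% retention, the number followed per arm is 0.75 × 80 = 60.

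| True rate p (assumed) | 16 interviewed | All 60 followed |
|---|---|---|
| 2% | 1 − 0.98^16 = 28% | 1 − 0.98^60 = 70% |
| 5% | 1 − 0.95^16 = 56% | 1 − 0.95^60 = 95% |
| 10% | 1 − 0.90^16 = 81% | 1 − 0.90^60 = 99.8% |

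**Step 3: what zero reports would exclude.** The one-sided 95% upper limit is 1 − 0.05^(1/n). For n = 16 it is 17.1%; for n = 60 it is 4.9%.

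Steps 2 and 3 treat the patients as a random sample and as independent. The interview sample is purposive, so its figures show scale only.

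**Step 4: what a two-arm comparison could show.** This takes 60 per arm, two-sided 5% level, and 60 / 8 = 7.5 patients per practice. The design effect at ICC 0.05 is 1 + (7.5 − 1) × 0.05 = 1.325.

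| Harm rates (assumed) | Power, no clustering | Power, ICC 0.05 |
|---|---|---|
| 5% vs 10% | 18% | 14% |
| 5% vs 20% | 70% | 58% |

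Asking everyone makes a rate and a comparison possible, but does not make a test of uncommon harms worthwhile.

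**Step 5: practitioner sources side by side.** Ethical Considerations says interviews. Timeline says self-administered questionnaires. Table 1 says free text in questionnaires. Qualitative Evaluation says open-ended questions. Three places agree with each other and differ from the fourth, and the topics they list do not name harm.

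**The case against.** The strongest reply is that this is a declared pilot of a 10–15 minute intervention, not powered even for effectiveness, and that exploring harms qualitatively is a reasonable choice at this stage. The interviews are analyzed thematically and were never meant to estimate incidence, so detection probabilities are a harsh yardstick. This is fair, and is why the figures above are only indicative. It does not answer the lack of any control counterpart.

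A reader might infer that harm cannot be detected or attributed at all in this trial. The documents do not support that. Sixteen interviews would probably show a harm affecting 10% or more of patients. AUDIT and MAP are completed in both arms at T1 and T2, so worsening drinking, drug use or health can be compared between randomized groups. For the same reason it would be wrong to say that controls contribute no relevant data. What stands is that the article does not assign these measures to harm.

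A reader might also infer that interviews are the trial's only safety procedure. The article does not say so, and a full protocol may hold adverse-event procedures that an article commonly leaves out. Nor does the Introduction say that the intervention causes relapse or medical complications; it attributes these to problem alcohol use.

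On practitioners, the mismatch may be loose wording: Qualitative Evaluation allows even patient interviews to be done by postal questionnaire. Free text on experience of the intervention could also bring unwanted effects to light. Both are possible, but the sections still disagree and harm is not a listed topic.

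**Conclusion.** The concern holds in a limited form. The assessment that the article designates for adverse effects cannot give or compare a harm rate, because on the patient side it rests on about 16 purposively chosen intervention-arm patients. Its practitioner half cites interviews that three other places describe as questionnaires with no listed harm topic.

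At an assumed 5% rate, the interviews have roughly an even chance of including one case, against about 95% if every followed intervention patient were asked. This depends on 1:1 allocation, 75% retention, the assumed rate and treating the sample as random. No conclusion follows that harm is undetectable in the trial as a whole or that comparative data are absent. The two-arm data exist and have not been put to this use. It is an inexpensive improvement worth making, not a flaw that undermines the feasibility aims.

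**What to change.** 1. Add one short adverse-effect item, worded identically, to the T2 patient questionnaire in both arms. It should ask about unwanted changes since baseline, not about effects of the intervention, so that controls can answer it.
2. Add one item on unwanted effects to the practitioner T2 questionnaire.
3. Report T1-to-T2 worsening in MAP substance use and in MAP physical and psychological health as harm outcomes, descriptively by arm, with the number of patients answering.
4. Reconcile Ethical Considerations with Timeline, Table 1 and Qualitative Evaluation, so that each names the same sources. Keep the patient interviews for context and explanation.

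The cost is one item on each of two existing questionnaires and one descriptive table, with slight added burden on patients and practitioners. The pilot will still have little power to compare uncommon harms, so the results should be given as counts and proportions, without a test, and a small difference between arms should not be read as evidence of safety.
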